### Plans to give access to the full protocol, participant-level data, and statistical code {31c}

This paper provides the full study protocol. Metabolomics data will be deposited in the NIH Common Fund’s National Metabolomics Data Repository (NMDR) website, the Metabolomics Workbench, and accessible directly via its project number following publication. Analytic code will be publicly and freely available without restriction at GitHub. Other data will be made available upon request pending review by the study principal investigators.

### Composition of the data monitoring committee, its role and reporting structure {21a}

The dietary interventions, biospecimen collections, and other outcome assessments pose minimal risk to participants. Thus, a data monitoring committee was not formed for this study, as no serious adverse effects are expected. The site PI ([name]) is a physician and provides frequent monitoring. In addition, study staff regularly monitor for adverse effects and/or undesirable symptoms, which can be reported using a case report form on REDCap.

### Adverse event reporting and harms {22}

Adverse event information is captured on a case-by-case basis in real time. All protocol violations and adverse events will be logged on a case report form in REDCap and reviewed and evaluated by the study PI, who is an MD, within 72 h. Serious adverse events will be evaluated by the PI within 24 h. Prompt reporting of excessive protocol violations, adverse events, or serious adverse events to COMIRB and the NIH will be conducted as needed.

### Frequency and plans for auditing trial conduct {23}

The trial is monitored continually by the study PI, postdoctoral fellow, and other study staff during biweekly clinical trial meetings as described above. An annual report is submitted to COMIRB for continuing review, and an annual progress report is submitted to the study sponsors (NIH and NCBA).

### Plans for communicating important protocol amendments to relevant parties (e.g., trial participants, ethical committees) {25}

Any protocol changes that impact study procedures or risk to human subjects (e.g., changes to eligibility criteria) will be submitted for approval by COMIRB and reflected in a revised consent form that will be reviewed and signed by all active participants. Protocol changes will also be amended in ClinicalTrials.gov and reported to NIH in annual progress reports.

### Dissemination plans {31a}

Study findings will be shared primarily via publication in peer-reviewed scientific journals and via national and international scientific conference oral and/or poster presentations. All journal articles will be submitted to PubMed Central (PMC) per the NIH Public Access Policy. Additional results will be disseminated via University of Colorado Anschutz Medical Campus social media channels and/or the lay press for the general population. All data will be available as described in the “Plans to give access to the full protocol, participant-level data, and statistical code {31c}” section. No data with personal identifiers will be published as part of this clinical trial.

## Discussion

This will be the first study to prospectively assess FSCs identified via metabolomics analysis of a completed MED controlled feeding intervention in an independent cohort. FSCs from target foods consumed within a complex background habitual dietary pattern will be assessed as putative biomarkers of intake to these foods as well as explored as potential biomarkers of effect by examining associations with cardiometabolic health indicators and microbiome community structure and function. This will achieve the important step of validation of FSCs for a large panel of foods within a complex dietary background which, to our knowledge, has not been performed. Such evaluation is critical for the rigorous development and testing of dietary biomarkers and will catalyze the advance in knowledge of the role of dietary patterns, specific foods, and individual compounds on the physiology of metabolic health outcomes. Strengths include a rigorously designed randomized, multi-intervention dietary intervention with provision of target foods of interest to encourage participant adherence. Frequent and intentional sampling of multiple biospecimen types (blood, urine, stool) aligning with dietary intake data and clinical assessments will allow for detailed assessment of the relationships between dietary intake, FSCs, and cardiometabolic health indicators.

Upon completion of this study, we will have tested a stepwise strategy to serve as a first step in validation of candidate biomarkers of food intake within dietary patterns, allowing for assessment of associations with cardiometabolic health indicators and thus laying the groundwork for future studies designed to assess uptake and depletion kinetics, dose–response, reproducibility, and interindividual variability. The resulting insights will enable us to inform definitive trials with improved clinical study design in the short term and implement precision nutrition interventions in the long term. The identification of biomarkers that link dietary intake to clinical status and biological functions is critical to future research in the following areas: vulnerable populations, including women of reproductive age and their offspring; comparisons of food- vs. supplement-based interventions; holistic treatment of diseases including cancer, HIV, and lung disease; diet-centric microbiome research; and food/agricultural science. We envision application of emerging technology to allow measurement of pre-identified FSCs in field-friendly platforms (e.g., blood spot cards). Such tools would allow investigations to monitor adherence and to identify responders and non-responders to beneficial food(s) and dietary patterns. Finally, with increasing recognition of the need for more sustainable dietary patterns, identification of FSCs to assess nutritional quality will be critical.

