Our results support the use of unmetabolized FSCs in either plasma or urine as candidate biomarkers of food intake. However, evaluation of multiple biospecimen types (e.g., blood and urine) simultaneously may increase coverage by collecting complementary information about different aspects of food metabolism [18]. Thus, collection and analysis of multiple biospecimen types will provide more comprehensive compound lists to define metabolomic signatures for testing associations with health indicators. Our preliminary results need to be prospectively tested within an independent intervention, a necessary next step for evaluation of reproducibilty and potential validation as biomarkers of food intake. Notably, our previous nutrimetabolomics research has been conducted within fully controlled feeding trials, making it difficult to elucidate the effects of incremental shifts between an “unhealthy” habitual/Western dietary pattern toward “healthy” evidence-based dietary patterns such as DASH or MED. The current mini-MED clinical trial study design and extensive biospecimen sampling plan directly address these limitations.

We are conducting a 16-week randomized, multi-intervention, semi-controlled feeding study among individuals with overweight/obesity who do not habitually consume a MED dietary pattern to comprehensively evaluate the reproducibility of FSCs using our innovative nutrimetabolomics approach. The novel FSCs identified in our eight MED target foods will be evaluated in participant biospecimens to assess change after intervention and to validate associations with cardiometabolic health indicators in this prospective semi-controlled feeding trial. The overall scientific premise is that FSCs will be reproducibly found when individuals consume specific foods, will not be found when individuals do not consume those foods, and will be associated with beneficial indicators of cardiometabolic health. In addition, we will evaluate the reproducibility of FSCs from beef in the context of different backgrounds (MED vs habitual/Western foods). Based upon existing literature, exploratory analyses will also be conducted to identify shifts in microbiome structure/function in response to incremental dietary changes.

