### Trial design {8}

This trial is a 16-week randomized, multi-intervention, semi-controlled feeding study of Mediterranean-amplified (mini-MED) and habitual/Western-style (Western) isocaloric dietary interventions containing 500 kcal/day from target foods. Participants are randomized (1:1) to start either the mini-MED or the Western dietary intervention, with subsequent assignment to the other upon completion of the first. Each 4-week intervention (mini-MED and Western) is repeated once. The Western intervention serves as both a washout of the mini-MED foods and a negative control for the postprandial response when the mini-MED foods are not consumed. Within the mini-MED arm, participants are further randomized to first receive salmon (mini-MED salmon) or lean, unprocessed beef (mini-MED beef) as a protein source, with consumption of the alternate protein source in their second mini-MED intervention period (Fig. 1). Outcome measures and biospecimen sampling take place at baseline and intervention weeks 4, 8, 12, and 16, and outcomes will be assessed using an exploratory approach.

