#### Intervention description {11a}

The dietary interventions are as follows: (1) Mediterranean-amplified (mini-MED) diet, containing 500 kcal/day from Mediterranean target foods: avocado, basil, cherry, chickpea, oat, red bell pepper, walnut, and salmon or lean, unprocessed beef as a protein source, and (2) habitual/Western (Western) diet, containing 500 kcal/day from non-Mediterranean target foods: cheesecake, chocolate frozen yogurt, refined grain bread, sour cream, white potato, and lean, unprocessed beef. Each intervention is 4 weeks, with a 2-week washout after enrollment but prior to initiation of the first dietary intervention (Fig. 1). Furthermore, each intervention is repeated to evaluate reproducibility within individuals over time.

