#### Criteria for discontinuing or modifying allocated interventions {11b}

No modification of the dietary interventions is permitted, and participants are asked to consume all provided study foods in prescribed amounts for the duration of the study. Participants may voluntarily withdraw from this study at any time for any reason. Furthermore, the principal investigator (PI) may decide to suspend a participant’s participation for any reason, (e.g., if he/she/they refuses to participate in any required study procedures, no longer meets study inclusion criteria, or is lost to follow-up).

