### Assignment of interventions: allocation

#### Sequence generation {16a}

All participants complete the mini-MED and Western dietary interventions twice each for four total intervention periods. Participants are randomized (1:1) to start either the mini-MED or Western dietary interventions, with subsequent assignment to the other upon completion of the first. A second randomization within the mini-MED arm is conducted to allocate participants to order of consumption of either salmon or lean, unprocessed beef as a protein source resulting in a total of four possible intervention orders (Fig. 1). Lean, unprocessed beef is consumed as the protein source in both Western intervention periods. A permuted block randomization scheme and stratification by sex has been generated and is utilized to ensure balance between intervention order and number of males and females. The allocation sequence was generated using computer-generated random number sequence in R using the *sample* command in *base* R package.

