## Statistical methods

### Statistical methods for primary and secondary outcomes {20a}

Assessment of the primary outcome of change in FSCs will be completed using the intercept of linear mixed effects models (LMMs) with change in FSCs (post–pre) as the outcome and a random intercept to control for repeated measures. Analysis will be stratified by mini-MED and Western interventions since we expect FSCs to increase during the mini-MED arm and to decrease during the Western arm. FSCs that significantly increase during the mini-MED interventions and significantly decrease during the Western interventions will be considered validated. We will adjust for multiple testing using false discovery rate (FDR) for the number of FSCs [37]. We will complete stratified analysis by intervention period to assess reproducibility of FSCs in increase (mini-MED) and decrease (Western). The relationship between cardiometabolic health indicators and diet intervention will be assessed using LMMs similar to that described above. The relationship between cardiometabolic health indicators and FSCs will be assessed using LMMs over all intervention periods with an interaction term for FSCs and diet (i.e., mini-MED, Western) to capture differential effects by diet.

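### The rise/fall rule tests response to the mini-MED food set as a whole and not the food label of the 355 plant-food candidate compounds, so the Discussion's claim of validation for a panel of foods goes too far

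*Protocol article*

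**What the plan says.** The premise in Background and rationale {6a} is stated food by food: "FSCs will be reproducibly found when individuals consume specific foods, will not be found when individuals do not consume those foods". The Discussion carries this through to the conclusion: "This will achieve the important step of validation of FSCs for a large panel of foods within a complex dietary background".

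Intervention description {11a} gives the mini-MED foods as "avocado, basil, cherry, chickpea, oat, red bell pepper, walnut, and salmon or lean, unprocessed beef as a protein source". They come as a fixed set: "No modification of the dietary interventions is permitted, and participants are asked to consume all provided study foods in prescribed amounts" (Criteria for discontinuing or modifying allocated interventions {11b}). Trial design {8} describes the off phase: "The Western intervention serves as both a washout of the mini-MED foods and a negative control". The only food varied within mini-MED is the protein, "with consumption of the alternate protein source in their second mini-MED intervention period". For the Western periods, Sequence generation {16a} adds: "Lean, unprocessed beef is consumed as the protein source in both Western intervention periods".

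On the analysis, Statistical methods {20a} says: "Analysis will be stratified by mini-MED and Western interventions". A compound counts as validated if it rises significantly over the mini-MED periods and falls significantly over the Western periods, after false discovery rate adjustment. The rule contains no contrast between foods and no measure of intake of the compound's own food.

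**The concern.** A food-level claim needs some contrast in which one food changes while the others stay put. For the seven plant foods the design has none. If a compound labelled basil in fact comes from chickpea, is present in several of the foods, or shifts because the Western foods were dropped, it follows the same on/off schedule as a true basil compound. The rule would then validate it under the basil label.

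What is at stake is the meaning of a pass. The end of the Discussion looks ahead to using pre-identified compounds to monitor adherence and to identify responders to particular foods. A wrong label would be carried into that use with the word validated attached.

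**Working it through.** **Inputs.** Plasma counts per food from Table 1: cherry 30, avocado 136, red bell pepper 27, basil 112, walnut 23, chickpea 17, oat 10, salmon 143, beef 76. The figure of 355 compounds from Sample size {14}. Food assignment from Trial design {8}, Intervention description {11a} and Sequence generation {16a}.

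**1. The plan's own figure.** Seven plant foods: 30 + 136 + 27 + 112 + 23 + 17 + 10 = 355. This equals the 355 in Sample size {14}. Adding the proteins: 355 + 143 + 76 = 574. Plant share: 355/574 = 61.8%. Leaving beef out: 355/(355 + 143) = 355/498 = 71.3%. The total of 574 is derived; the protocol does not state it.

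**2. Assigned exposure by type of period** (1 = supplied, 0 = not supplied):

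| Period | Each of the 7 plant foods | Salmon | Beef | Other Western foods |
|---|---|---|---|---|
| mini-MED salmon | 1 | 1 | 0 | 0 |
| mini-MED beef | 1 | 0 | 1 | 0 |
| Western (twice) | 0 | 0 | 1 | 1 |

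The four randomised orders (S = mini-MED salmon, B = mini-MED beef, W = Western) are S-W-B-W, B-W-S-W, W-S-W-B and W-B-W-S. Over these 4 × 4 = 16 order-by-period cells:

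- The seven plant columns are identical, so together they have rank 1: one joint contrast for seven foods. With 20 completers this holds at all 20 × 4 = 80 period-ends.
- All nine mini-MED food columns together have rank 3: one for the plant block, and salmon and beef.
- Salmon + beef = 1 in every period, so the two proteins are exact complements.
- Other Western foods = 1 − plant block. A rise over mini-MED is therefore also compatible with removal of the Western foods.

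**3. The rule applied to a compound labelled with plant food A.** If it comes from A, its source is on in mini-MED and off in Western. If it comes from plant food B, or from both, the schedule is the same. If it responds to the dietary pattern as a whole, the schedule is again the same. For a given size of response, the chance of passing does not depend on which of these is true. The planned analysis by intervention period repeats the same joint contrast, so it adds evidence on reproducibility but not on the label.

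**4. What the protein switch adds.** Subtract the table rows, mini-MED salmon minus mini-MED beef: plant foods 1 − 1 = 0, other Western foods 0 − 0 = 0, salmon 1 − 0 = +1, beef 0 − 1 = −1. The plant block and the Western foods cancel, leaving the salmon effect minus the beef effect. This within-person contrast separates the proteins from the plant foods, but not fully from each other. The rule in {20a}, which groups periods only as mini-MED or Western, pools over it.

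**5. Beef under the rule.** Moving from mini-MED salmon to Western restores beef, and moving from mini-MED beef to Western leaves it unchanged. Neither move gives the fall over Western that the rule requires of a beef compound.

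**The case against.** The strongest reply is that the rule is not asked to attribute compounds to foods. Background and rationale {6a} describes prior metabolomics of more than 100 foods aimed at compounds unique to a food, and Objectives {7} tests pre-defined compounds for response to intake and reproducibility within persons. That stands. The test of response is not wrong. The label, however, is inherited, and the trial does not check it. The earlier plasma detections also came from people eating complex meals within a whole diet, and participants here keep an otherwise self-chosen diet.

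Secondly, the claim is softened elsewhere. The Abstract and the closing paragraph of the Discussion call the trial a first step towards validating candidate biomarkers, the sentence before the quoted one calls them putative, and Trial design {8} calls the assessment exploratory. This also stands, and it makes the quoted sentence and the bare word validated in {20a} the outliers to be aligned.

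Thirdly, no rate of mislabelling is shown. That is right: 355 counts candidates exposed to the problem and does not count errors.

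Fourthly, 3-day food records will capture intake of target foods, and an analysis plan not shown may model them. Their absence from the rule is no omission in itself. But the plant foods are prescribed at fixed amounts, about 5 to 7 servings a week in Table 2, and 20 completers give 20 × 2 = 40 visits at the end of a mini-MED period. Variation would come mainly from non-adherence and from which foods fell on the recorded days, so such a model is at most weak support.

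A reader might infer that the plan declares all 355 compounds validated for their foods. It does not: only those meeting the rule count. A reader might also infer that salmon and beef are clean food-specific cases. Steps 4 and 5 of the working show that they are not. Objectives {7} does frame a separate hypothesis for beef, stability across dietary backgrounds, but {20a} states no validation rule to match it.

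**Conclusion.** The point holds in a limited form. For the seven plant foods the rule tests one joint contrast, the mini-MED food set against the Western set. A pass shows response to that set. It does not independently confirm the food label, and the Discussion sentence claims more than the rule can deliver and more than the protocol's own first-step wording.

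The reach is 355 of 574 candidate plasma compounds (62%), assuming that no compound is counted under two foods in Table 1. The number actually mislabelled, shared or pattern-driven is unknown and may be small if the prior uniqueness screen was good. The aliasing refers to assigned foods; actual intake will vary somewhat, but not by design. No planned test statistic is shown to be wrong. What needs changing is the meaning attached to a pass, the use made of the randomised protein switch, and the rule for beef.

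**What to change.** 1. In Statistical methods {20a} and in the Discussion, state that a pass for a plant-food compound means it is responsive to the mini-MED food set, with attribution to the named food resting on the prior food analysis. Bring the Discussion sentence into line with the Abstract and the closing paragraph.
2. Add the within-person randomised contrast between the salmon and beef mini-MED periods. Salmon compounds should be higher in the salmon period, beef compounds higher in the beef period, and plant compounds should not differ. Report estimates with intervals, since a non-significant difference in about 20 people is not proof of none. State that salmon and beef are exact complements, so the contrast separates them from the plant foods but not fully from each other. It also cannot detect a mix-up between two plant foods.
3. State that the rise/fall rule does not apply to beef compounds, because beef is eaten in both Western periods, and judge them on the contrast in item 2 and on the stability hypothesis in Objectives {7}.
4. If a model on recorded own-food servings is fitted, label it as weak supporting evidence.

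The cost is some wording and one added contrast on data already being collected, with no new participants, visits or samples. The downside is a narrower claim for the plant foods.

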## Trial status

This study protocol is based on version date August 24, 2023. The study was open to accrual on August 5, 2022, and recruitment is ongoing. It is anticipated that recruitment will be completed in January 2024.

The approved informed consent documentation will be provided upon request.

## Data Availability

Only the study team will have direct access to the final analyzed data. As described above, metabolomics data will be deposited Metabolomics Workbench and accessible directly via its project number. Analytic code will be publicly and freely available without restriction at GitHub. Other data will be made available upon request pending review by the study principal investigators.

## Abbreviations

ADOPT: Accumulating Data to Optimally Predict obesity Treatment
ASA24®: Automated Self-Administered 24-h Dietary Assessment Tool
BIA: Bioelectrical impedance
BMI: Body mass index
CDC: Centers for Disease Control and Prevention
COMIRB: Colorado Multiple Institutional Review Board
CTRC: Clinical and Translational Research Center
DASH: Dietary Approaches to Stop Hypertension
FMV: First morning void
FSC: Food-specific compound
HDL: High-density lipoprotein
HIPAA: Health Insurance Portability and Accountability Act
LDL: Low-density lipoprotein
MD: Medical doctor
MED: Mediterranean
NCBA: National Cattleman’s Beef Association
NIH: National Institutes of Health
NMDR: National Metabolomics Data Repository
PERMANOVA: Permutation-based analysis of variance
PGP: Phosphatidylglycerol phosphate
PHA: Personal health assessment
PI: Principal investigator
PMC: PubMed Central
RD: Registered dietitian
REDCap: Research Electronic Data Capture
TG: Triglyceride
USDA: United States Department of Agriculture
